### Sample size calculation

The size of the study was based on the primary outcome measure HbA1c. According to a power calculation, an absolute difference of 1.0% in HbA1c between the GSD-Y group and the control group (power 0.8; two-sided level of significance 0.05) could be detected with 26 patients in each group. This calculation was based on a standard deviation of the HbA1c value of 1.3% from a study of coping skills training [45]. To compensate for an attrition rate of 25%, we aimed to recruit 68 patients.

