#### Secondary outcome a

Danish versions of 6 scales were compiled in one questionnaire (Table 4). The questionnaires will be completed by the adolescents at the outpatient clinics and placed in a closed envelope before being returned to the personal HCPs at the following timepoints: 1) baseline before randomisation, 2) after the end of the intervention/control period (8-12 months), and 3) after a 6-month follow-up period (ranging between 14 and 18 months from the time of entry into the trial).

**Table 4 T4:** Adolescent measures and outcome

**Scales**	**Outcome**	**Ranging**	**Examples**	**Scores**
The Perceived Competence Scale (PCD) 5-item	Experience of own competence	Ranging from 1 (strongly disagree) to 7 (strongly agree)	*"I feel confident in my ability to manage my diabetes"*	Produces a total sum score from 5- 35. A high sum score represents a high level of perceived competence

The Health-Care Climate Questionnaire (HCCQ) 5 -item	Perceptions of autonomy support from HCP	Ranging from 1 (strongly disagree) to 7 (strongly agree)	*"I feel that my HCPs have provided me choices and options about handling my diabetes"*	Produces a total sum score from 5-35. A high sum score represents a high level of perceived autonomy support

The Treatment Self-Regulation Questionnaire (TSRQ) 21-item Consists of 3 subscales	The degree in which patients' behaviour is self-determined	Ranging from 1 (strongly disagree) to 7 (strongly agree)	*(I) Autonomous; "It's exciting to try to keep my blood sugar in a healthy range"* *(II) Controlled; "I want my HCP to think I am a good patient"* (III) A-motivated; "I do not know why I do try - I will not bee successful"	Produces sum scores for each of three subscales, Autonomous from 8-56, Controlled 9-63, Amotivated 4-28. High sum scores indicate high levels of autonomy, controlled or amotivated behaviour. A Relative Autonomy Index is calculates by subtracting the controlled scores from the autonomous scores. The higher relative autonomy index the higher is motivation based on autonomy compared to control

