### Analysis

To meet Objective 2 and test if GSD-Y effectively reduces HbA1c and improves life skills in adolescents with type 1 diabetes, we will analyse HbA1c and quantitative data from the questionnaires using PAWS Statistics18 for Windows (SPSS Chicago, IL, USA). Statistical analyses will include frequency, mean, standard deviation and confidence intervals. Comparisons of primary and secondary outcomes for the two groups will be conducted comparing data at baseline, at the end of the study, and after a 6-month follow-up period using appropriate parametric tests for variables fulfilling the normal distribution criteria or appropriate non-parametric tests for variables not fulfilling the normal distribution criteria. A Bonferroni correction for multiple testing will be performed.

Improvement of life skills will be defined as increases in HCCQ-scores, TSRQ-scores on autonomy or in relative autonomy index (formed by subtracting TSRQ-scores on control from TSRQ-scores on autonomy), PCD, POPS, WHO-5 and frequency of SMBG per week, and decreases in TSRQ-scores on amotivation, PAID scores and HbA1c. Differences within the GSD-Y group and between the GSD-Y group and the control group will be calculated at the end of the intervention (8-12 months) and after a 6-month follow-up period.

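### The plan fixes a plain Bonferroni correction; Holm's step-down procedure gives the same family-wise error control, never rejects less, and rejects more when several scales respond

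*Protocol article*

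**What the plan says.** The Analysis section gives the multiplicity rule in one sentence: "A Bonferroni correction for multiple testing will be performed". The sentence before it sets the scope of testing: "Comparisons of primary and secondary outcomes for the two groups will be conducted comparing data at baseline, at the end of the study", and then again after the 6-month follow-up. The article does not say which of these comparisons form the corrected family or how many there are.

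The same section lists what counts as better life skills. It begins "Improvement of life skills will be defined as increases in HCCQ-scores, TSRQ-scores on autonomy or in relative autonomy index", goes on to PCD, POPS, WHO-5 and the frequency of self-monitored blood glucose, and ends with "decreases in TSRQ-scores on amotivation, PAID scores and HbA1c". Differences within the GSD-Y group and between the groups "will be calculated at the end of the intervention (8-12 months) and after a 6-month follow-up period". Confidence intervals are planned as well.

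The Sample size calculation rests on HbA1c alone, with "power 0.8; two-sided level of significance 0.05" and no allowance for multiplicity.

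**The concern.** The life-skills half of Objective 2 rests on a set of secondary scales in a trial sized for HbA1c only. Once a correction is applied to that set, power for each scale is low. A procedure that gives the same protection against false positives and can only add rejections is therefore preferable for the p-value decisions.

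The gain could matter here because the theory behind GSD-Y expects autonomy support, relatedness and competence to improve together. Effects on several scales are thus the working hypothesis, and that is the situation in which a step-down procedure helps.

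**Working it through.** **Inputs from the protocol article.** Two-sided alpha 0.05, power 0.8, HbA1c difference 1.0%, SD 1.3%, 26 per group, 25% attrition, 68 recruited (Sample size calculation).

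**Assumptions not in the article.** Number of tests m = 10 (also 8 and 20), pairwise correlation 0.4 (also 0, 0.3 and 0.5), and the effect sizes on the scales. Ten is a plausible count. Taking HbA1c out of the life-skills list leaves HCCQ, TSRQ autonomy, relative autonomy index, PCD, POPS, WHO-5, glucose monitoring, TSRQ amotivation and PAID, which is nine. Splitting POPS into mother and father makes ten, and two post-baseline time points make 20.

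**1. The plan's own figure.** n per group = 2 × (1.960 + 0.842)² × 1.3² / 1.0² = 26.5, so 27 against the stated 26. Power at 26 is 0.79. Attrition: 52 / 0.75 = 69.3, so 70 against the stated 68. The figures agree to within two patients. The planned effect is 1.0 / 1.3 = 0.77 SD.

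**2. The two rules at m = 10.** Bonferroni tests every p-value at 0.05/10 = 0.005. Holm orders the p-values and tests the j-th smallest at 0.05/(10 − j + 1), stopping at the first failure. The thresholds are 0.005, 0.05/9 = 0.0056, and so on up to 0.05/1 = 0.05. The first equals Bonferroni's and the rest are larger, so no Bonferroni rejection can be lost. The chance of at least one rejection is the same for both.

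**3. Why the gain depends on how many scales respond.** If k scales truly respond and the other k − 1 have been rejected, the last is tested at 0.05/(10 − k + 1). That is 0.005 for k = 1 (no change), 0.05/6 = 0.0083 for k = 5, and 0.05 for k = 10.

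**4. Simulated mean power per affected scale** (two-sample t-tests, 26 per arm, m = 10, correlation 0.4, 5,000 trials per setting):

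| Scales affected | Effect | Bonferroni | Holm |
|---|---|---|---|
| all 10 | 0.8 SD | 48.8% | 60.6% |
| all 10 | 0.6 SD | 23.3% | 29.0% |
| all 10 | 0.5 SD | 13.8% | 16.7% |
| all 10 | 0.4 SD | 7.8% | 9.2% |
| 5 of 10 | 0.8 SD | 48.0% | 51.3% |
| 5 of 10 | 0.6 SD | 23.1% | 24.7% |
| 5 of 10 | 0.5 SD | 14.8% | 15.8% |

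With eight scales, all affected, the figures are 50.9% against 62.3% at 0.8 SD and 25.6% against 31.5% at 0.6 SD.

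**5. Sensitivity** (correlations 0, 0.3 and 0.5). With one affected endpoint the gain is 0.0 to 0.1 points. With m = 20 and 0.77 SD it is 6.7 to 9.6 points if all respond and 2.4 to 2.8 points if half do. With m = 20 and 0.5 SD it is at most 2.1 points.

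**6. Error control.** With no true effects, the family-wise error was the same for both methods in every setting, from 0.036 to 0.050.

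**The case against.** The strongest reply is that nothing is wrong. Bonferroni is valid under any dependence, contradicts nothing in the article, and yields simultaneous confidence intervals directly, which suits a plan that reports intervals. A full analysis plan that is not shown may also define the family and the procedure. All of this stands, and it is why the point is only a suggestion.

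The reply is also right about size. The largest gains need nearly all scales to respond at about 0.77 SD or more. The article gives no expected effect on any scale, and 0.8 SD is slightly above even the planned HbA1c effect.

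Three stronger readings are tempting, and the document supports none of them.

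- *Holm will often be clearly more powerful.* The table shows gains of about 1 to 3 points when half the scales respond and about 3 points at 0.5 SD even when all do.
- *Bonferroni is the wrong choice because the scales are correlated.* Some dependence is built in, since the relative autonomy index is "formed by subtracting TSRQ-scores on control from TSRQ-scores on autonomy", but the article states no correlation. Holm does not use correlation either. With no true effects, m = 10 and correlation 0.5, both methods have a family-wise error of 0.040.
- *The plan puts HbA1c inside the corrected family.* The preceding sentence mentions the primary outcome, but no family is named.

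The reply does not touch the central fact: for p-value decisions Holm gives up nothing in error control and cannot lose a rejection.

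**Conclusion.** The point holds as an efficiency improvement of low priority. That Holm controls the same family-wise error and never rejects less is exact and needs no assumption. The size of the gain does need assumptions. At 26 per arm with ten scales correlated at 0.4, it is about 12 points of mean power per scale if all respond at 0.8 SD, 6 points if all respond at 0.6 SD, 3 points if all respond at 0.5 SD or half respond at 0.8 SD, and practically nil if one responds. The number of tests, the correlation and the effects are not in the article. A reader might infer that the planned analysis is invalid or that its conclusions are at risk; neither follows.

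**What to change.** Replace the multiplicity sentence with wording such as: *The secondary between-group comparisons, at the end of the intervention and at the 6-month follow-up, will be corrected by the Holm step-down procedure at 5% family-wise error. The primary HbA1c test will be carried out at an unadjusted two-sided 0.05.*

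The Holm family should hold the same secondary between-group comparisons that would otherwise receive Bonferroni. The follow-up tests must be named, so that changing the method does not leave them uncorrected.

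The HbA1c clause keeps the analysis in line with the sample size. Were HbA1c tested at 0.05/10, its normal-approximation power at 26 per group would be 0.49 instead of 0.79, and Holm would repair little of that unless most other endpoints also showed large effects. If the authors did mean to correct HbA1c, this clause changes the scope: the primary test and the secondary family each carry 5%, so the error across both is bounded by 0.05 + 0.05 = 0.10.

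The change costs a sentence or two and no data. The real downside is the intervals: Holm has no simple matching simultaneous ones, so ordinary 95% intervals would stand beside Holm-adjusted p-values and may sometimes exclude zero where the adjusted p-value exceeds 0.05. The report should say so.

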**Methods/Design:**

Using a mixed methods design comprising a randomised controlled trial and a nested qualitative evaluation, we will recruit 68 adolescents age 13 - 18 years with type 1 diabetes (HbA1c > 8.0%) and their parents from 2 Danish hospitals and randomise into GSD-Y or control groups. During an 8-12 month period, the GSD-Y group will complete 8 outpatient GSD-Y visits, and the control group will completes an equal number of standard visits. The primary outcome is HbA1c. Secondary outcomes include the following: number of self-monitored blood glucose values and levels of autonomous motivation, involvement and autonomy support from parents, autonomy support from HCPs, perceived competence in managing diabetes, well-being, and diabetes-related problems. Primary and secondary outcomes will be evaluated within and between groups by comparing data from baseline, after completion of the visits, and again after a 6-month follow-up. To illustrate how GSD-Y influences glycaemic control and the development of life skills, 10-12 GSD-Y visits will be recorded during the intervention and analysed qualitatively together with individual interviews carried out after follow-up.

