## Background

Type 1 diabetes in adolescents is a challenge for the teenagers, their parents and the diabetes health care providers (HCPs) [1]. Despite new medical treatment modalities, the prognosis for childhood-onset type 1 diabetes remains poor [2,3]. The number of life years lost remains unchanged over the last four decades at approximately 17 years for a child diagnosed with type 1 diabetes at the age of 10 years [4]. Keeping blood glucose levels as close to normal as possible from as early in the disease as possible is known to prevent or postpone late diabetic complications [5-8]. The recommended target for haemoglobin A1c (HbA1c) in adolescents with type 1 diabetes is less than 7.5% without increasing the occurrence of hypoglycaemia [9]. However, adolescents typically do not maintain the necessary degree of diabetes self-management or the recommended HbA1c levels [10,11]. In Denmark, 31% of affected adolescents meet the recommended HbA1c threshold [12]. Although late diabetic complications are rarely seen during adolescence, there is evidence that their pathogenesis begins soon after diagnosis and accelerates during puberty [13,14].

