### Enrolment

#### Inclusion criteria

All adolescents aged 13-18 years who have had type 1 diabetes for more than one year will be invited to participate together with their parents if they meet the following criteria:

▪ HbA1c ≥ 8.0% at the last visit before entry into the study and

▪ Average HbA1c > 7.5% during the last year before entry into the study.

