### Data Collection, Measurements and Analysis Quantitative component

#### Primary outcome

HbA1c will be collected as a routine clinical measurement every third month, which is a standard practice. The capillary blood samples for HbA1c from both hospitals are being analysed at the same department of clinical biochemistry using Variant Analysis Mode, TOSOH Automated Glycohaemoglobin Analyzer HLC-723 G8 (normal range 4.3% - 5.8%).

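### Outcomes are also to be evaluated within the GSD-Y group, where selection on high HbA1c can produce an apparent fall without any effect; conclusions should rest on the between-group difference

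*Protocol article*

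**What the plan says.** The Abstract (Methods/Design) announces that "Primary and secondary outcomes will be evaluated within and between groups", using data from baseline, the end of the visits and the 6-month follow-up. The Analysis section narrows this: "Differences within the GSD-Y group and between the GSD-Y group and the control group will be calculated", at 8-12 months and again at follow-up. It names no within-control difference. The same section defines improvement of life skills as increases in a list of scores "and decreases in TSRQ-scores on amotivation, PAID scores and HbA1c". The definition gives a direction of change but does not say compared with what.

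Two entry criteria select on the primary outcome. The first concerns the most recent value: "HbA1c ≥ 8.0% at the last visit before entry into the study". The second concerns the longer record and reads: "Average HbA1c > 7.5% during the last year before entry into the study". The article does not say whether the baseline HbA1c is the qualifying value or a new sample. It does say that "HbA1c will be collected as a routine clinical measurement every third month".

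The hypothesis in the Background, the sample size calculation and the one Analysis sentence that mentions tests are all about GSD-Y against control.

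**The concern.** A group chosen because its most recent HbA1c was high will tend to show lower values on remeasurement, treated or not. In a single arm that fall cannot be told apart from an effect of GSD-Y. Change within one arm also contains any time trend and the effect of eight visits in 8 to 12 months, which the control arm's equal number of visits is there to remove.

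The text names a within-GSD-Y contrast for HbA1c, defines improvement without a comparator, and does not say which contrast carries the conclusion. A report could therefore describe a significant fall within GSD-Y as evidence of effectiveness while the randomised comparison shows nothing.

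**Working it through.** **Inputs from the protocol.** SD of HbA1c 1.3% and 26 evaluable per group (Sample size calculation); last value at least 8.0% and yearly average above 7.5% (Inclusion criteria); quarterly measurement (Primary outcome); 31% of Danish adolescents with type 1 diabetes meeting the recommended threshold of 7.5% (Background).

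**The plan's own figure.** Per group, n = 2 × [1.3 × (1.960 + 0.842) / 1.0]² = 26.5, within one patient of the stated 26. It is a between-group calculation and is not affected by this point. It only supplies the n = 26 used below.

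**Assumptions not in the protocol.** Normal HbA1c; visit-to-visit correlation r from 0.6 to 0.9; a clinic mean inferred by joining the national 31% to the SD of 1.3%. The SD comes from a coping-skills study, and neither figure describes these two clinics.

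**Step 1, clinic mean.** The normal quantile for 31% is −0.496, so the mean is 7.5 + 0.496 × 1.3 = 8.14%.

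**Step 2, closed form for the single cutoff.** The cutoff lies at (8.0 − 8.14)/1.3 = −0.11 SD. The ratio of density to upper tail there is 0.728. Selected values exceed the mean by 1.3 × 0.728 = 0.947 on average, and the expected fall is 0.947 × (1 − r):
- r = 0.6: 0.38
- r = 0.7: 0.28
- r = 0.8: 0.19
- r = 0.9: 0.09

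**Step 3, both entry criteria.** I simulated four quarterly values per adolescent (stable level plus independent visit noise), applied both criteria, used the qualifying value as baseline, and gave no treatment effect. The rate columns show how often a paired t test in 26 adolescents is significant in favour of GSD-Y. The nominal rate in that direction is half of alpha.

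| r | mean fall | SD of change | rate, alpha 0.05 | rate, alpha 0.005 |
|---|---|---|---|---|
| 0.6 | 0.35 | 1.09 | 35% | 10% |
| 0.7 | 0.26 | 0.96 | 27% | 6% |
| 0.8 | 0.17 | 0.79 | 19% | 4% |
| 0.9 | 0.09 | 0.57 | 12% | 2% |

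Hand check at r = 0.6: 0.35 × √26 / 1.085 = 1.64. The critical value is 2.06, and P(Z > 2.06 − 1.64) is about 0.34, close to the simulated 35%. The 0.005 column stands for a Bonferroni family of ten tests, an assumption because the article does not define the family.

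**Step 4, the randomised contrast.** In the same simulated trials, the two-sided test of change between two such arms rejected in about 5% at every r. Between 10% (r = 0.9) and 33% (r = 0.6) of null trials had a significant within-arm fall together with a non-significant between-group difference (uncorrected 0.05).

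**Step 5, sensitivity to the baseline.** If baseline is a fresh sample and visit noise is independent, the mean fall is 0.00 and the rate is 2.5%. If baseline is fresh but successive visits are serially correlated (clinic mean 8.2%, stable share of variance 0.5 to 0.7, quarterly autocorrelation 0.5 to 0.8), the fall is 0.12 to 0.22 and the rate 9% to 20%.

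**The case against.** The strongest reply is that the trial is built on the randomised contrast. The hypothesis is comparative, the sample size rests on a between-group difference, and the only sentence naming tests concerns comparisons of the two groups. The Analysis section says that within-GSD-Y differences will be calculated; it names no within-group test and no decision rule. This stands. A reader might infer that effectiveness will be judged on within-arm change, on equal footing with the randomised comparison, or that the benefit of randomisation is given up. The text does not go that far. It leaves the ranking unstated.

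A reader might also infer that selection necessarily produces a fall, or that the trial's main comparison is biased. Neither is supported. The fall depends on which sample is baseline and on the correlation between visits, and the article gives neither. The bias falls equally on both arms, so it cancels in the comparison.

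Further limits stand:
- Only HbA1c is an entry criterion, so the regression argument does not apply directly to the questionnaire scales.
- A time trend could run upward and offset the fall: the Background cites a teamwork intervention whose benefit was to prevent worsening.
- The planned Bonferroni correction lowers the false-positive rates, though it leaves the biased estimate in place.
- Whether within-group tests would use up part of that correction cannot be said, because the family of tests is not defined.
- The largest plausible fall is near the 0.4% reported for GSD in adults but well below the planned 1.0%.

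What survives is that a named contrast and a comparator-free definition of improvement are in the text as it stands. They are not details deferred to another document.

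**Conclusion.** The point holds in a limited form. The plan names a within-GSD-Y contrast and defines improvement without a comparator, in adolescents selected for a high last HbA1c. With the qualifying value as baseline, a clinic mean near 8.1% and r from 0.6 to 0.9, all assumed, regression to the mean alone can give a fall of 0.35 to 0.09 points. A one-arm paired test would then favour GSD-Y in about 35% to 12% of null trials at uncorrected 0.05, or 10% to 2% at 0.005. With a fresh baseline and independent noise the bias is zero. The flaw touches only conclusions drawn from within-arm change; the between-group analysis and the sample size stand. For the questionnaire outcomes the objection is only the absence of a control. This is a worthwhile clarification of wording and does not threaten the trial's validity.

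**What to change.** In the Abstract (Methods/Design) and the Analysis section, state that conclusions about effectiveness for HbA1c and for life skills rest on the between-group difference at each timepoint (end of intervention and 6-month follow-up), adjusted for the baseline value already collected. Tie the definition of improvement to that difference. Report within-group change descriptively for both arms, with means and spread but no significance tests. This changes wording and one model term. It needs no new data, no further patients and no change to the sample size.

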### Qualitative component

#### Data collection

Ten to twelve adolescents from the intervention group and their parents and HCPs will be followed during the intervention period. To ensure that we follow triads who face significant challenges, we will select them on the basis of high PAID scores and low WHO-5 scores at baseline, which indicate difficulties with life skills.

Data will be collected during the intervention period by recording two or three outpatient appointments between 1) adolescent, parent and HCP, 2) adolescent and HCP, and 3) parent and HCP.

Individual interviews will be carried out and recorded with the above-mentioned triads after the intervention's endpoint measures at a 6-month follow-up visit using a semi-structured interview guide [72] prepared on the basis of both listening to the recordings from outpatient visits and the definition of life skills [57,73].

